## Abstract

**Background:**

The working environment should be a naturally integrated part of business development. Provisions are in place that address the employer’s obligations to investigate, carry out and follow up activities in such a way that ill health and accidents at work are prevented and a satisfactory working environment is achieved. Still, there are organizations that not properly perform systematic work environment management. In order to improve adherence, interventions and models focused on these issues need to be easy to understand and provide rapid feedback of results in order to be implemented. The Stamina model has recently been implemented in Sweden. The model is a participatory organizational systematic model facilitating the work environment, productivity and quality. It is a support model that provides structured and recurrent feedback in the systematic work environment management. The aim of the present paper is to thoroughly describe the Stamina model and the studies that are designed to investigate the effect, to increase the understanding of how and why the model was or was not effective, and to identify factors that facilitate implementation.

**Methods:**

The paper presents a project consisting of two related evaluation parts. Part one is an effect evaluation with an active group applying the Stamina model and a control group. This part investigate effects on proxy outcomes that are relevant for health and productivity. Part two is a process evaluation with a qualitative design. This part will be based on semi-structured interviews with various stakeholders, such as employees, first line managers, project managers, facilitators and representatives from the management group, in the organizations.

**Discussion:**

Many interventions found to be effective in research projects fail to translate into meaningful outcomes across multiple contexts. In this project a participatory approach will be adopted, including the possibility to modify the model according to organizational needs and preconditions. Valuable knowledge regarding the design and implementation of the model will be generated in order to develop a model that is suitable and sustainable in organizations.

**Electronic supplementary material:**

The online version of this article (10.1186/s12889-018-5807-9) contains supplementary material, which is available to authorized users.

## Background

Work-related illnesses and accidents are issues that cannot be neglected in society because they have great consequences for both the individual worker [1] and the employer [2]. On a global level, it is estimated that 317 million people suffer from work-related illness and accidents annually [2]. In the late 1980s, employers’ responsibility was clarified in a European directive stating that employers are required to assess risks to the safety and health of workers, and to implement measures aimed at reducing the identified risks [3]. The working environment should be a naturally integrated part of organizational development. National legislation regulating employees’ health and safety at work varies across countries around the world. In Sweden, there is the provision of Systematic Work Environment Management (AFS 2001:1) [4], which addresses employers’ obligations to investigate, carry out and follow up activities in such a way that ill health and accidents at work are prevented and a satisfactory working environment is achieved. Although this guideline is available, it has been reported that there are still organizations in Sweden that do not properly perform their systematic work environment management [5]. These findings might be interpreted in light of other research showing that interventions focused on these issues need to be easy to understand and adopt in the organization if they are to be implemented [6], and it is known that the Systematic Work Environment Management provision is often experienced as time-consuming and somewhat abstract [7–9]. Furthermore, it is also known that health preventive workplace interventions that lack rapid feedback on results causes organizations to be less interested in focusing on work environment management [6]. Another key to successful implementation of interventions focused on systematic work environment management is the engagement of first-line managers, because they are in the position and have opportunities to influence the work environment by providing support to employees [10]. It is well-known that the support given by first-line managers positively influences employees’ job satisfaction, work engagement [11] and perceived work environment [12]. However, central initiatives taken in organizations do not always reach first-line managers and their work groups.

Nielsen and colleagues [13] compiled an overview of five European methods/interventions aimed at improving employee health and wellbeing using systematic approaches. They identified five phases with certain elements that are of importance for an effective intervention. These phases are: preparation, screening, action planning, implementation and evaluation. Organizational readiness for change [14] and effect evaluation are examples of important elements [13]. Furthermore, it has been found that employee participation was an overarching theme that was apparent in all phases and elements [13, 15]. It has been emphasized that, to promote employee participation, employees’ involvement needs to be in place already in the preparation phase [13]. Employee participation have also been highlighted in terms of being involved in problem-solving and decision-making to promote mental health at work [16].

The Stamina model has recently been implemented in Sweden in order to concretize systematic work environment management. Stamina is an acronym for “Structured and Time-effective Approach through Methods for an INclusive and Active working life”. The model that builds upon the Model of Integrated Group Development [17, 18] has a participatory systematic approach aimed at improving the work environment, productivity and quality. It is a support model that provides structured and recurrent feedback in the systematic work environment management. Evaluating a model focused on the organizational level – and involving employee participation as a central part and direct engagement from organization stakeholders – entails some challenges; for example, the researcher has less control over the action that is taken. Still, the Stamina model deliberately takes this stance, which has been supported in previous research showing that work environment management interventions often are complex organizational interventions that need to be adapted to the specific organization. Even though such adaptations are made, it is possible to conduct an effect evaluation using a controlled design [19]. It might also be appropriate to broaden the focus from solely providing knowledge on effectiveness to generating knowledge that could guide forthcoming actions based on a certain model/intervention [20] as well as to increase the understanding of why and how the model/intervention is or is not perceived as effective [21]. Such an approach will provide opportunities for organizations to continue to adapt the efforts and actions to their real-world context. To generate useful knowledge about such flexible models from research, it is important to thoroughly describe the framework of the actual model, and the context for the study.

The aim of the present paper is to thoroughly describe the Stamina model and the studies that are designed to investigate the effectiveness of the Stamina model, as well as why and how this model is or is not experienced as effective.

## Methods/design

The paper presents a project consisting of two related evaluation parts. The aim of the first part, the effect evaluation, is to investigate effects on proxy outcomes that are relevant for health and productivity. The aim of the second part, the process evaluation, is to increase the understanding of how and why the intervention was or was not effective, and to identify factors that promote implementation of the Stamina model.

The study is approved by the Regional Ethics Committee in Uppsala, Sweden (Reg. No. 2017/093).

### The Stamina model

The description of the Stamina model is inspired by the template for intervention description and replication (TIDieR checklist) [22].

#### Materials and procedures used in the Stamina model

The basic principle of systematic work environment management and organizational development is that it should be a perpetual, repetitive process for improvement. The idea behind the development of the Stamina model is that it should facilitate employee participation and rapid and recurrent feedback to the first-line managers and their work groups. The work process in the Stamina model is owned by the organization and is not dependent on any external consultants or researchers. In practice, this means that organizations can arrange their work in various ways, leading to some modifications of the model. One example is that the sessions within the model might be delivered either by a facilitator or a first-line manager, or by these two actors together. This approach makes the actions taken by the organizations less controlled than is typical in this kind of research. Some elements are still fixed and these will be presented below.

The Stamina model sessions are delivered three times annually during the project’s two-year duration. The first session (workshop) lasts for approximately 3 h and the second and third sessions (follow-ups) for 1 h each. The sessions are held at four-month intervals. All three sessions are preceded by a web-based questionnaire measuring Human Resource Index (HRI). The basic question reads “What characterizes your current work situation” and includes an evaluation scale indicating whether the factors are positive or negative and a scale indicating whether the respondent can influence the situation. All employees answer the question with free text and, thus, have the opportunity to emphasize aspects they feel are the most important at that moment. Reports are generated, based on these questionnaires, and serve as working material to support the work group’s reflections and discussions during the sessions.

The first session (workshop) consists of: 1) reflections on the shared basic values, aims and goals of the work group, 2) reflections on the work group’s current work situation, 3) reflections on how the work group wants their work situation to be, and 4) reflections on what actions can be taken to create the desired work situation. In the last step, the work group prioritize one activity they want to focus on and create an action plan based on a manual. The second and third sessions (follow-ups) include a review of previous action plans and creation of new ones.

#### Description of the expertise and specific training given to the providers

In the Stamina model, the workshops are delivered by facilitators working in the participating organizations. It is the organizations that decide which persons that is eligible for the role of facilitator. These persons might, for example, work at a central Human Resource unit within the organization or closer to the specific work groups. Having the opportunity to choose who will be the facilitators increases the feasibility of and adherence to the model in the organization. The two follow-ups are led by the facilitator or the first-line manager in the organization, with support from the facilitator.

The facilitator attend a two-day course to learn how to lead the workshop and how to support the participants in creating the action plans. Between the two course days, the facilitators conduct a pilot workshop in which they practice their role as moderator/facilitator of the session. On the second day, their experiences from the workshop are discussed and reflected upon. The first-line managers do not receive any specific training other than videos with instructions on how to run the sessions. They always have the opportunity to ask and discuss specific issues with the facilitators.

#### Mode of delivery

The sessions in the Stamina model are provided to a group of employees, all of whom work together. The size of the groups depends on the number of employees included in the work groups, which may vary across the organization types targeted. Approximately 8–20 employees is an acceptable size for a group.

The sessions are held at the participants’ own workplaces. The first-line managers choose a suitable room for the sessions in collaboration with the facilitator.

#### Tailoring of the Stamina model

The sessions take a generic approach during the first year to enable the participating organizations to learn the structure and overarching content of the sessions. This is the same for all participants/work groups. However, tailoring is built into the intervention, as a variety of activities are identified and in focus during the work with action plans. Furthermore, the Stamina model during year two can be tailored so as to be feasible in practice for the organizations and work groups. This tailoring may involve, for example, a change in the person leading the workshop (from facilitator to first-line manager) or in session length. Such tailoring is built into the model to facilitate long-term sustainability and implementation adapted to different organizations. However, the content of each session from year one should be retained.

### Part 1 - effect evaluation

#### Study design

This is a quantitative study with a non-randomized waiting-list pre-post trial design. Work groups are assigned to either a control group that only answers to the web-based questionnaire that is the first action within the model or to an active group that conduct all parts included in the Stamina model. The control group that only answer the web-based questions will be given the opportunity to conduct all parts of the model at a later point.

#### Aim and research questions

The aim of this evaluation is to investigate effects on proxy outcomes that are relevant for health and productivity in the active and control group. These proxies are HRI, perceived productivity, organizational justice and sleep.Research questions include the following:How are HRI, perceived productivity, organizational justice and sleep changing over time in the active and control group?What characterizes groups with high and low HRI at the start of the intervention?What types of focus areas are identified in the groups?Does HRI correlate with sleep and organizational justice in the work groups?

#### Study sample

Municipalities in Sweden are eligible for the study. Recruitment of municipalities that are eligible to participate in the project will be a country-wide process. The eligible municipalities will be selected so as to achieve variation in number of employees and geographical conditions. Approximately 20 municipalities will be included in the STAMINA project.

Before the municipalities make their final decision regarding participation, they will be involved in a pre-programme focused on establishing commitment, preparation and planning [13]. The programme includes a lecture on work environment, establishing commitment in the respective organizations and discussions with the research group.

Based on the perspective that the project has its point of departure in the real-world context, the participating municipalities have the opportunity to choose the number of employees included in the project. The number of employees might vary between 100 and 1000. Employees representing approximately 20% of the total number of employees using the model in each municipality will be allocated to the control group. This control group size will be sufficient to detect general trends in the study population. A power calculation of the study groups with the given sample sizes, estimated standard deviation of 29 and a power of 0.8 will detect a difference of mean of HR index at 0.9 units.

The study sample will consist of work groups applying the model in their systematic work environment management. That is, no information regarding the individual employees will be analysed. Demographics will be presented regarding the work groups characteristics. Considering the preliminary numbers of municipalities and employees included in the project, the study sample is estimated to include between 500 and 1800 work groups in the group working according to the Stamina model.

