#### Analysis

Statistical methods adapted to a non-randomized waiting-list controlled pre-post trial design will be applied. HRI is an estimate of group resilience and a predictor of future health status in work groups and is also used as guidance for group development. Given the emphasis on the work group, all analyses will be performed at the group level, where each work group is treated as one unit/individual. Repeated measures will be analysed using generalized linear models to detect changes over time.

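### The stated detectable HRI difference of 0.9 units does not follow from the plan's own SD, sample sizes and 20% control share in an unadjusted between-arm comparison, and it does not fit the work-group analysis

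*Protocol article*

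**What the plan says.** All the inputs are in the protocol article, Part 1 (effect evaluation), unless noted.

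- Study sample, power statement: "estimated standard deviation of 29 and a power of 0.8 will detect a difference of mean of HR index at 0.9 units". The sentence refers to the given sample sizes but names no unit, number per arm, alpha or sidedness. It directly follows a sentence that judges the control group large enough to show broad trends.
- Study sample, size: "Approximately 20 municipalities will be included in the STAMINA project", and for each municipality "The number of employees might vary between 100 and 1000".
- Study sample, allocation: "Employees representing approximately 20% of the total number of employees using the model in each municipality will be allocated to the control group".
- Study sample, work groups: "the study sample is estimated to include between 500 and 1800 work groups in the group working according to the Stamina model". The same paragraph adds that "no information regarding the individual employees will be analysed".
- Analysis: "all analyses will be performed at the group level, where each work group is treated as one unit/individual".
- Mode of delivery (description of the model): "Approximately 8–20 employees is an acceptable size for a group".
- Human resource index: HRI runs from 0 to 100 and is described as reflecting an individual's perception.

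**The concern.** An SD of 29 on a 0 to 100 scale is very wide, and 0.9 is about 3% of that SD (0.9/29 = 0.031). Detecting so small a standardised difference between unequal arms takes tens of thousands of independent units. The plan has at most about 20,000 employees and about 2,250 work groups, and the work groups are what it will analyse.

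HRI is the first-named outcome and the only one with a power statement. Readers will take 0.9 as the study's sensitivity, and as support for the neighbouring statement that a 20% control group is enough. If the figure is wrong, that support goes, and a result showing no difference could be given more weight than the design can bear.

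**Working it through.** **Inputs.** SD 29, power 0.80 and the stated difference of 0.9 come from Study sample. Total employees are 20 × 100 = 2,000 to 20 × 1000 = 20,000. The control share is about 20%, read as 80:20. Active work groups number 500 to 1800, so controls at 80:20 number 500/4 = 125 to 1800/4 = 450. Assumed: alpha 0.05 two-sided, so z = 1.9600 + 0.8416 = 2.8016.

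**Formula.** Detectable difference = 2.8016 × SD × √(1/n_active + 1/n_control).

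**1. Trying to reproduce 0.9 with employees as independent units, SD 29.**
- 16,000/4,000: 29 × √(1/16,000 + 1/4,000) = 0.5127; × 2.8016 = **1.44**. One-sided 5% gives 1.27, and one-sided 10% gives 1.09.
- 1,600/400: 29 × √(1/1,600 + 1/400) = 1.621; × 2.8016 = **4.54**.
- Controls read as 20% of the active number, 20,000/4,000: 1.41 two-sided, 1.25 one-sided.
- Size needed for 0.9 at 80:20: controls = 1.25 × (2.8016 × 29/0.9)² ≈ 10,187, so 5 × 10,187 ≈ 50,900 employees. That is about 2.5 times 20,000. One-sided, it is about 40,100.

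**2. Work groups as units, SD 29.**
- 1800/450: 2.8016 × 29 × √(1/1800 + 1/450) = **4.28**.
- 500/125: 2.8016 × 29 × √(1/500 + 1/125) = 2.8016 × 29 × 0.1 = **8.12**.

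**3. Group-level SD that would give 0.9.**
- 1800/450: 0.9/(2.8016 × 0.0527) = 6.1.
- 500/125: 0.9/(2.8016 × 0.1) = 3.2.

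If 29 is an individual SD, independent members in groups of 20 give a group-mean SD of 29/√20 = 6.5. That is still above 6.1, before any within-group correlation.

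**4. Illustration of a group-level answer (ICC assumed).** SD of a group mean = 29 × √(ICC + (1 − ICC)/m), with m = 8 to 20 and ICC = 0.05 to 0.2.

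| Groups (active/control) | Most favourable: ICC 0.05, m = 20 (SD 9.06) | Least favourable: ICC 0.2, m = 8 (SD 15.88) |
|---|---|---|
| 1800/450 | 1.3 | 2.3 |
| 500/125 | 2.5 | 4.5 |

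The 1.3 needs 2,250 groups of 20, that is 45,000 employees, which is above the 20,000 ceiling. At 20,000 employees those groups average about 8.9 members, and the range becomes 1.7 to 2.3.

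**5. Where 0.9 does appear.**
- Two equal arms of 16,000 employees: 0.908.
- A one-sample change with SD 29: 2.8016 × 29/√8,150 = 0.90.

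Neither compares the arms at the planned split.

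**The case against.** Several other routes lead to or near 0.9.

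- **Change over time within the active group.** Analysis refers to change over time, and Discussion mentions comparisons over time within the Stamina group. A one-sample change reaches 0.9 at about 8,150 employees, which lies within the plan's range. A reader might infer that 0.9 can only come from assuming equal arms; this shows that the documents do not establish that. But a calculation without the control arm cannot support a statement about control-group size, and it still counts employees.
- **A larger ceiling.** 1800 groups of 20 is 36,000 active employees. With 9,000 controls the detectable difference is 0.96 two-sided and 0.85 one-sided. This exceeds the plan's 20 × 1000 employees and ignores clustering.
- **Baseline adjustment.** The design is pre-post. At 16,000/4,000, a pre-post correlation of about 0.78 (ANCOVA) or 0.80 (change score) would bring 1.44 down to 0.9. No correlation is stated, and the unit would again be the employee.
- **Little depends on 0.9.** No margin or decision rule is tied to it, municipalities choose their own enrolment, and the adequacy statement speaks only of general trends. This stands, and it limits the consequence. It does not make the figure correct.

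Condensation into an article is no answer either: the figure conflicts with inputs printed in the same section.

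**Conclusion.** The stated 0.9 units is not supported. For an unadjusted between-arm comparison with SD 29, 80% power and about 20% controls, the plan's sizes give 1.44 to 4.54 units with employees as independent units and 4.3 to 8.1 with work groups. Alpha is assumed to be two-sided 5%; no level tried, including one-sided 10%, brings the 20,000-employee case (16,000/4,000) down to 0.9.

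Three stronger readings go beyond the documents:

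- A reader might take it as fact that 0.9 was computed on employees. The unit is not stated. It is a strong inference, because SD 29 with 0.9 needs tens of thousands of units in a two-arm comparison. On the other reading, with work groups as units, 0.9 is too small by a factor of about 5 to 9 (4.28/0.9 to 8.12/0.9).
- A reader might quote the study's power for 0.9 as 42% (16,000/4,000) or 8% (1,600/400). Those values hold only for an unadjusted, single-time comparison of independent employees, which is not the planned repeated-measures analysis of work groups.
- A reader might treat the range in step 4 as the true detectable difference. It rests on assumed ICCs and shows only the likely direction and order of size.

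**What to change.** Replace the 0.9 sentence in Study sample with a work-group calculation that states:

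- the unit of analysis;
- the numbers of active and control work groups at the planned split;
- alpha and sidedness;
- the SD of work-group mean HRI, taken from existing HRI data or the baseline round;
- any pre-post correlation used.

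Report the detectable difference at both ends of the 500 to 1800 range. The illustrative values in step 4 should not be used as protocol text. Then re-justify or withdraw the statement that the 20% control group is sufficient, in light of the new figure.

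This costs one rewritten paragraph and a less favourable stated figure. Enrolment need not change.
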